## Abstract

**Background::**

The aim of this study is to compare the postoperative quality of life (QoL) and survival outcomes in lower rectal cancer (LRC) patients who undergo either laparoscopic- intersphincteric resection or extralevator abdominoperineal excision (L-ELAPE) after long-course neoadjuvant chemoradiation therapy (nCRT).

**Methods::**

This prospective, single-center, non-randomized, controlled, non-blinded, phase I/II clinical trial is designed to enroll 159 eligible LRC patients who achieved favorable response to long-course nCRT (2 × 25 Gy). After informed consent, the patients will be assigned into the laparoscopic intersphincteric resection group or L-ELAPE group according to their own will. Standard radical laparoscopic surgeries will be performed for every participant. Then every participant will be followed up for 3 years. The primary outcomes are scores of QoL questionnaire-core 30, QoL questionnaire-colorectum 29, Wexner incontinence score, International Prostate Symptom Score (for male), International Index of Erectile Function-5 (for male) and Female Sexual Function Index (for female). The secondary outcomes consist of incomplete circumferential resection margin rate, 3-year local recurrence, 3-year disease-free survival, 3-year overall survival and other surgical outcomes.

**Discussion::**

This is the first prospective clinical controlled trial to assess postoperative QoL and efficacy for LRC patients after favorable long-course nCRT. The result is expected to provide new evidence for a more detailed individualized treatment guideline for LRC.

**Trial registration::**

This trial was registered at Chinese Clinical Trial Registry (*ChiCTR1800017512*; ChiCTR.org) on August 2, 2018.

## Introduction

1

Colorectal cancer is the fourth most commonly diagnosed malignancy and the second predominant cause of cancer-related death worldwide.^[1]^ According to the data from the International Agency for Research on Cancer (IARC), rectal cancer would rank 8th in terms of incidence, accounting for approximately 40% of Colorectal cancer and constituting a severe global public health burden. Surgery is still the cornerstone of curative intent treatment for rectal cancer.^[2]^ Without regard to lower rectal cancer (LRC), it is undoubtful that anterior resection (AR) is the preferred surgical procedure for mid-upper rectal cancer.^[3]^ Abdominoperineal excision (APE) firstly reported by Ernest Miles in 1908 has long been considered the “gold standard” surgical management for LRC.^[4,5]^ Proven unappealing oncologic outcomes in APE compared to AR from several large-scale case series on resected rectal specimen, Holm et al presented a new approach of extended APE, also known as extralevator APE (ELAPE), without waist to reduce the risks of circumferential resection margin (CRM) involvement and intraoperative perforation for advanced tumors.^[6–8]^ Since Schiessel et al proposed their initial experience with intersphincteric resection (ISR) for LRC,^[9]^ a promising alternative to APE without permanent colostomy, the indication for ISR has been gradually assessed and strictly applied. Meanwhile, laparoscopic-assisted minimally invasive surgery is expected to allow meticulous precise operation with good visualization in narrow pelvic cavity.^[10]^

However, with the widespread adoption of neoadjuvant chemoradiation therapy (nCRT), management of LRC has shifted significantly.^[11,12]^ Yet, whether ultimate sphincter-preserving procedures, such as ISR, offer equal or better oncologic outcomes to LRC patients after favorable response from nCRT becomes controversial compared to APE or ELAPE.^[13,14]^ Surgery for LRC has to maintain a balance between radical tumor removal to minimize the risk of locoregional recurrence and patients’ desire, or postoperative quality of life (QoL).^[15,16]^ Postoperative continence is one of important outcome measures of QoL for LRC patients, and there are conflicting reports on the functional outcomes and QoL for patients after ISR compared to APE.^[16–19]^

Thus, the aim of our trial is to prospectively compare QoL, perioperative complications and oncologic outcomes of laparoscopic intersphincteric resection (L-ISR) with laparoscopic extralevator abdominoperineal excision (L-ELAPE) in the patients with LRC after significant response to nCRT. The results are expected to provide new evidences for more detailed individualized therapies for LRC.

## Methods

2

### Study design

2.1

The study protocol follows the standard protocol items: recommendation for interventional trials (SPIRIT) guidelines.^[20]^ This is a prospective, single-central, non-randomized, non-blinded, phase I/II clinical controlled trial. All eligible patients will be assigned into 2 comparison groups (the L-ISR group and the L-ELAPE group) according to their own will after detailed preoperative conversations. The flow diagram of this trial is shown in Figure 1. Our trial started from September 2018 in West China Hospital of Sichuan University and is expected to end in 2021.

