#### Follow-up and dropping out

2.3.2

All participants will be followed up regularly as per schedule (Table 1) every 3 months for the first 3 years after surgeries. If necessary, biopsy and MRI will be performed to assess local or distant recurrence.

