### Outcome measures

2.4

The primary outcomes of this trial are to be scores of European Organization for Research and Treatment of Cancer QoL questionnaire-core 30 (QLQ-C30), QoL questionnaire-colorectum 29 (QLQ-CR29), Wexner Incontinence Score, International Prostate Symptom Score (for male), International Index of Erectile Function-5 (for male) and Female Sexual Function Index (for female). General QoL is assessed basically by scores of European Organization for Research and Treatment of Cancer QLQ-C30 version 3.0^[24]^ and QLQ-CR29.^[25]^ Defecation functions (daily defecation, frequency, urgency, incontinence, differentiation between defecation and gas emission, pad use, antidiarrheal drug use, and the presence or absence of erosion around the anus) are evaluated by the Wexner Incontinence Score.^[26]^ Sexual function for men and women is assessed by using the International Index of Erectile Function-5^[27]^ and Female Sexual Function Index,^[28]^ respectively. Urinary function is assessed by using the International Prostate Symptom Score^[29]^ for men and color ultrasonography of residual urine volume for all.

The secondary outcomes include incomplete CRM rate, 3-year local recurrence, 3-year disease-free survival, 3-year overall survival, and other surgical outcomes. Incomplete CRM is defined as tumor within 1 mm from closest mesorectal fascia, or within 1 mm from closest levator muscle, or invasion into or beyond the insphincteric plane. Local recurrence is defined as recurrent disease in the pelvis or at the incision. Disease-free survival is defined as the time of surgery to recurrence or end of follow-up. Overall survival is defined as the time of surgery to the date of death from any cause or the end of follow-up. Surgical outcomes include operation time, intraoperative blood loss, temporary stoma, intraoperative perforation, time to first flatus, time to liquid diet intake, postoperative hospitalization days, postoperative complications, incidence of urinary retention, and postoperative mortality in 30 days.

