### Sample size

2.5

This is a non-inferiority verification study with QoL and efficacy as the main index. In the pilot study, incomplete CRM rate was 6.1% (2 out of 33 patients) in the L-ELAPE group. Based on the previous studies, we assume that the rate of incomplete CRM in the L-ISR group was 8.1% which was the average value in the meta-analysis.^[30]^ The adjusted formula below is used to calculate the sample size^[31]^ (Fig. 2). The “Pe” and “Pc” are the rates of incomplete CRM of the experiment group and the control group, respectively. The “k” represents the ratio of 2 groups’ sample sizes which equals 1 in this trial and “p” represents the joint probability. Setting type I error probability **α** = 0.025, type II error probability **β** = 0.2, the sample size required for each group is 72 cases. Furthermore, we assume that there will be a 20% dropout rate. Therefore, at least 159 patients are needed in this specific trial.

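### A September 2018 start and an expected end in 2021 leave about 4 months to operate on all 159 participants if each is to have 3 years of follow-up

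*Protocol article*

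**What the plan says.** Section 2.1 (Study design) gives the calendar: "Our trial started from September 2018 in West China Hospital of Sichuan University", and the trial "is expected to end in 2021".

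The follow-up commitment appears twice. The Abstract (Methods) says: "Then every participant will be followed up for 3 years". Section 2.3.2 (Follow-up and dropping out) applies to all participants and counts from the operation, with visits "every 3 months for the first 3 years after surgeries".

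Section 2.4 (Outcome measures) lists "3-year local recurrence, 3-year disease-free survival, 3-year overall survival" among the secondary outcomes. It lets disease-free and overall survival time run to the end of follow-up when no event occurs. Section 2.5 (Sample size) sets the enrolment: "Therefore, at least 159 patients are needed in this specific trial".

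On capacity, section 2.1 describes a single center and section 2.3.1 (Interventions) names two operating surgeons. No accrual period or monthly rate is given.

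**The concern.** A trial that gives each participant 36 months after surgery cannot finish sooner than 36 months after the last operation. The stated start and end are at most 40 months apart, so almost the whole calendar is taken up by one participant's follow-up and very little is left for recruitment.

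What is at stake is the basis of the 3-year estimates. If follow-up runs to 36 months for everyone, local recurrence, disease-free survival and overall survival at 3 years rest on complete observation apart from dropout. If the trial closes in 2021, they may rest largely on administratively censored follow-up. The reader cannot tell which is planned. The closing date also sets other deadlines: section 2.7 ties release of individual patient data to trial completion, and section 2.8.2 counts data retention from the study's termination.

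**Working it through.** **Inputs from the protocol article**
- Start: September 2018 (section 2.1), taken as 1 September, the earliest possible date.
- End: 2021 (section 2.1), taken as 31 December, the latest possible date.
- Follow-up: 36 months from surgery for every participant (Abstract; section 2.3.2).
- Enrolment: 159 (section 2.5).

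The first two choices are the ones most favorable to the plan.

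**Step 1. Time available for surgery**
- Calendar: 1 September 2018 to 31 December 2021 = 40 months.
- Latest surgery that allows 36 months: 31 December 2018.
- Window: 40 − 36 = 4 months (121 days).

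An end in September 2021 would leave between zero and about one month.

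**Step 2. Pace required**
- 159 / 4 = 39.8 operations per month.
- 159 / (121 / 7) = 9.2 operations per week.
- Counting only the 72 per group of section 2.5 (144 in all): 144 / 4 = 36 per month.

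The only patient count from the center is a pilot L-ELAPE group of 33 (section 2.5), with no period attached, so it gives no rate. Eligibility is also narrow: tumor within 5 cm of the anal verge, and 6 to 12 weeks after long-course chemoradiation (section 2.2.1).

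**Step 3. Slower accrual with closure at the end of 2021**

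The accrual period A is an assumption, since the document gives none. Accrual is taken as uniform from 1 September 2018. Potential follow-up at closure then runs evenly from 40 − A to 40 months, so:
- share with at least t months of potential follow-up = min(1, (40 − t) / A);
- at t = 36 this is min(1, 4 / A);
- end date that gives everyone 36 months = start + A + 36 months.

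| A (months) | Operations per month | Last participant's follow-up at end of 2021 (months) | Share with 24 months | Share with 36 months | End needed for 36 months in all |
|---|---|---|---|---|---|
| 4 | 39.8 | 36 | 100% | 100% | December 2021 |
| 6 | 26.5 | 34 | 100% | 67% | February 2022 |
| 12 | 13.2 | 28 | 100% | 33% | August 2022 |
| 18 | 8.8 | 22 | 16/18 = 89% | 22% | February 2023 |
| 24 | 6.6 | 16 | 16/24 = 67% | 17% | August 2023 |

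These shares count administrative censoring only. Deaths and dropout would lower the numbers at risk further. The table shows where the loss falls: most participants are still covered at 24 months, and coverage drops steeply between there and 36 months.

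**The case against.** The strongest reply is that the end date is a forecast. Section 2.1 says only what is expected, whereas the follow-up rule is stated per participant in two places. No passage sets a data cut-off in 2021 or says that follow-up stops then. If the per-participant rule governs, the 3-year outcomes are obtained and only the projected date is wrong. This stands, and it is why the effect on the results is conditional on closure in 2021. It does not remove the mismatch, because nothing in the visible text says which statement governs.

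A reader might infer that the calendar makes 3-year follow-up impossible. The documents do not show that. Four months of accrual would fit, and doubt about 40 operations per month is a judgement about the capacity of one center with two surgeons. The accrual periods in the table are illustrations and do not describe this trial's recruitment.

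A reader might also infer that the 3-year estimates would rest on the few earliest participants alone. That goes too far. Section 2.7 plans Kaplan–Meier estimation, which uses each participant's time at risk up to censoring. Early censoring mainly costs precision in the late part of the curve.

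Nor can it be said that late quality-of-life assessments would be lost. Section 2.4 gives no assessment times for those scores, and Table 1, the follow-up schedule, is not shown. Figure 1 is not shown either and might carry an enrolment window. It is also possible that 2021 was meant as the end of enrolment, but the sentence speaks of the trial ending, so it would still need correcting.

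**Conclusion.** The point holds in a limited form. The stated calendar is compatible with 3 years of post-surgery follow-up for all 159 participants only if every operation fell within about 4 months, at about 40 per month, and the document gives no basis for that pace.

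If the trial closed at the end of 2021, everyone operated on after December 2018 would be censored short of 3 years. The share with 36 months of potential follow-up would be about 33%, 22% or 17% for accrual over 12, 18 or 24 months. Those figures rest on assumed uniform accrual and on the most favorable start and end dates. The consequence is imprecision in the late part of the local recurrence, disease-free survival and overall survival curves. The incomplete margin rate, which drives the sample size, and the early outcomes are not affected.

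Severity is moderate: the affected outcomes are secondary. It is more than a clerical matter, because the date decides whether those outcomes rest on complete or mostly censored follow-up.

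**What to change.** Reconcile section 2.1 with the Abstract and section 2.3.2:

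1. State the planned accrual period.
2. Define the end of study as the date of the last participant's surgery plus 36 months, in place of a calendar year.
3. Run the 3-year local recurrence, disease-free survival and overall survival analyses only after that date.
4. If 2021 was meant as the end of enrolment, say so and give the end of follow-up separately.

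If closure in 2021 is fixed, drop the promise of 3 years for every participant, report these outcomes to the horizon that follow-up supports, and show numbers at risk.

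The cost is a later final analysis. With 12 to 24 months of accrual from September 2018, follow-up would be complete between August 2022 and August 2023. No additional participants are needed.

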**Figure 1 F1:**
[figure not shown]
Flow diagram for the schedule of enrollment, interventions, and assessments. L-ISR = laparoscopic intersphincteric resection, L-ELAPE = laparoscopic extralevator abdominoperineal excision.

### Study population

2.2

#### Inclusion criteria

2.2.1

Age(years): 18 to 75Histologically confirmed rectal adenocarcinoma, such as well/moderately/poorly differentiated tubular, papillary, or mucinous adenocarcinoma, or signet-ring cell carcinoma, etcLower tumor margin is ≤5 cm from anal verge when diagnosed via colonoscopyClinical staging: cT_1–2_N_1–2_M_0_ or cT_3_N_0–2_M_0_ on high resolution magnetic resonance imaging (MRI) before nCRT (according to the 8th edition of AJCC/TNM staging system)Six to 12 weeks after long-course nCRT (2 × 25 Gy)Absence of multiple primary carcinomas or distant metastasisASA (American Society of Anesthesiologists) classification: I-IIIPerformance Status (Eastern Cooperative Oncology Group, ECOG) scores: 0 to 2Written informed consent.

#### Exclusion criteria

2.2.2

Age(years): younger than 18 or older than 75Past history of malignancyRectal cancer related complications (including acute obstruction, perforation, and bleeding) that requiring emergency operationsPast history of colorectal surgeries which may have impact on the reconstruction of digestive tract this timeInvasion or suspicious invasion of tumor into the adjacent structure, such as vagina, prostate, sacrococcyx, or lateral pelvic wallASA (American Society of Anesthesiologists) classification: IV-VPregnant or lactating womenSevere psychological disorderSevere emphysema, pulmonary fibrosis, ischemic heart disease (IHD), or other medically inoperableContinuous systematic steroid therapy within the past monthContraindications of laparoscopic surgery, MRI or radiation therapyPatients who cannot understand the requirements and aims of this trial.

### Interventions and follow-up

2.3

#### Interventions

2.3.1

After assignment, patients in the L-ISR group will undergo standard L-ISR surgeries, while patients in the L-ELAPE group will undergo standard L-ELAPE surgeries with no intraoperative position change. Prophylactic ileostomy will be performed for selected patients with higher risk of anastomotic leakage in the L-ISR group. The radical laparoscopic-assisted surgery with meticulous total mesorectal excision and pelvic automatic nerve preservation (PANP)^[21–23]^ will be performed independently by 2 experienced and highly-specialized surgeons from the Department of Gastrointestinal Surgery, West China Hospital. Adjuvant chemotherapy, consistent with the preoperative neoadjuvant chemotherapy strategy for every participant, will continue within 4 to 6 weeks following surgery till completing 8 cycles. Closure of the ileostomy will be performed within 3 to 6 months after L-ISR according to rigorous preoperative assessment by digital rectal examination, colonoscopy, and barium enema examination.

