### Randomization and blinding

2.6

Due to the specificity and ethics, it is unlikely that any surgical center around the world would randomize patients to receive either L-ISR or L-ELAPE due to a lack of equipoise regarding the requirement for each operation in any particular patient. Direct comparison by a randomized controlled trial of the 2 procedures is currently virtually impossible. This trial allows the surgeons and outcome assessors to be aware of the whole assignment and all eligible patients will be informed of the treatment in detail on admission to hospital. However, statisticians responsible for the final analyses will be blinded.

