### Data collection, management, and statistical analyses

2.7

For purpose of acquiring high-quality monitoring, we plan to employ several professional clinical investigators to collect and manage the data of all participants during entire trial performing. A Case Report Form (CRF) is designed for each participant to document their data. And we will upload the data of all participants to Research Manager (ResMan), an Electronic Data Capture (EDC) system, and the individual patient data (IPD) will be publicly accessed via Chinese Clinical Trial Registry (ChiCTR.org) within 3 years after completion of this trial.

SPSS for Windows, version 22.0 (IBM Corp, Armonk, NY) will be used for statistical analysis. The data are presented as the mean value **±** standard deviation for continuous variables and as a number for categorical variables. The difference of categorical data and continuous data will be compared with Student *t* test and chi-square test between the 2 groups, respectively. The Kaplan–Meier estimate will be used to analyze survival and fit survival curves. The multiple factor analysis will be performed by using Cox regression model.

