## Discussion

3

Currently, the hot issue of the treatment for LRC located within 5 cm from anal verge is still being debated worldwide. The rapid improvement of surgical techniques and devices and universal utilization of preoperative treatment brings not only opportunities to management of LRC but new challenges to overcome. There is much controversy, however, on a new question as to which surgical option is more appropriate for patients with LRC after favorable response to nCRT to obtain better postoperative QoL and survival outcomes.

Although recent reports suggest that ultimate sphincter-preserving procedures, including ISR, may be feasible to cure LRC without compromise of resection margins and subsequent survival outcomes,^[13,33]^ advanced surgical technique is indispensable for ISR to deliver oncologic efficacy. There is a steep learning curve to successfully completing the L-ISR or L-ELAPE operation, including precise knowledge of rectal anatomy and its anomalies, to avert injury to critical adjacent structures. Perineal wound complications will be attached great importance on and biomaterial as a novel alternative will be used for pelvic floor reconstruction in the L-ELAPE group of our study. As for ISR, anastomotic leakage and anastomotic stricture must be taken into further consideration.^[34,35]^ Thus, prophylactic ileostomy will be performed for selected patients with higher risk of anastomotic leakage and digital rectal examination monthly after surgery is necessary in the L-ISR group.

Given the evident psychological and social impact of permanent colostomy required by APE surgeries, ISR was developed to provide a sphincter-preserving alternative.^[36,37]^ However, recent studies have challenged the assumption that global QoL is worse in patients with permanent stomas (eg, ELAPE patients).^[18]^ A matched-pair analysis comparing the long-term functional outcomes and QoL for 2 post-surgical populations indicated that ISR was associated with higher frequency of diarrhea and constipation than APE.^[16]^ Postoperative continence is exactly an important clinical outcome for LRC patient. Therefore, the pros and cons of each procedure will be discussed with patients and their families before decision making in our study. Psychological guidance, incontinence and stoma care education, and instruction of sphincter exercises will be added into the follow-up for both groups.

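### The QoL and incomplete-CRM comparisons name only unadjusted tests that cannot account for which of two surgeons operated, in groups formed by patient choice with no stated rule on surgeon mix

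*Protocol article*

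**What the plan says.** Four statements in the protocol article bear on this point.

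- **Allocation** (2.1, Study design): there is no randomization. Patients enter a group "according to their own will after detailed preoperative conversations".
- **Operators** (2.3.1, Interventions): surgery in both groups "will be performed independently by 2 experienced and highly-specialized surgeons from the Department of Gastrointestinal Surgery". The article does not say whether each surgeon does both procedures, or how cases are shared between them.
- **Analysis** (2.7): the groups "will be compared with Student *t* test and chi-square test between the 2 groups, respectively". Read literally, that sentence pairs the t test with categorical data and the chi-square test with continuous data. I take the order as transposed, so that scores get the t test and incomplete CRM the chi-square test. Survival is analysed by Kaplan–Meier, and "The multiple factor analysis will be performed by using Cox regression model", with no covariates listed.
- **Operator skill** (3, Discussion): "There is a steep learning curve to successfully completing the L-ISR or L-ELAPE operation".

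The scores are the primary outcomes (2.4), and incomplete CRM drives the sample size (2.5). There, "incomplete CRM rate was 6.1% (2 out of 33 patients) in the L-ELAPE group" is the centre's own pilot result, while the 8.1% assumed for L-ISR is a meta-analysis average.

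**The concern.** In a randomized trial, two surgeons contributing to both arms would tend to balance out. Here the patient chooses after a conversation, and section 2.6 itself argues that equipoise is lacking about which operation a given patient needs. It is plausible, though not stated, that the surgeon a patient meets influences the choice. The surgeons' shares could then differ between groups.

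Margin status, perforation, blood loss, complications and nerve-dependent urinary and sexual function can all depend on the operator. An unadjusted comparison would credit any surgeon difference to the procedure. Adjusting for tumour and patient factors alone would not remove it. If each surgeon did only one of the procedures, no analysis could separate the two effects.

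**Working it through.** **The plan's own figures.** Pilot rate: 2/33 = 6.1%. Assumed L-ISR rate: 8.1%. Assumed gap: 8.1 − 6.1 = 2.0 points. Required number: 72 per group. I take 72 as given, because it depends on a non-inferiority margin that is not in the readable text. No figure in the article concerns the surgeons, so everything about them below is an assumption.

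**Step 1: the bias.** Let s₁ and s₂ be the proportions of the L-ISR and L-ELAPE groups operated on by surgeon A. Let D be the outcome difference between surgeons, taken as the same for both procedures. Then

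expected group difference = procedure effect + (s₁ − s₂) × D.

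The second term is the bias. It is zero if s₁ = s₂ or if D = 0. For incomplete CRM with D = 5 points:

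| Share difference | Bias |
|---|---|
| 0 points | 0 |
| 20 points | 0.20 × 5 = 1.0 point |
| 40 points (e.g. 70% against 30%) | 0.40 × 5 = 2.0 points |
| 60 points | 0.60 × 5 = 3.0 points |

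**Step 2: effect on the named tests.** Assume no true procedure effect, 72 per group and a two-sided 5% test.

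For a score in SD units, the standard error is √(2/72) = 0.167. With D = 0.5 SD and a 40-point share difference, the bias is 0.2 SD, or 0.2/0.167 = 1.2 standard errors. The rejection probability is 1 − Φ(1.96 − 1.2) + Φ(−1.96 − 1.2) = 22%.

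For incomplete CRM at the mean rate of 7.1%, the standard error is √(2 × 0.071 × 0.929/72) = 4.3 points. A 2-point bias is under half a standard error.

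| Share difference | Score, D = 0.3 SD | Score, D = 0.5 SD | CRM, D = 5 points |
|---|---|---|---|
| 20 points | 6.5% | 9% | 5.6% |
| 40 points | 11% | 22% | 7.5% |
| 60 points | 19% | 44% | 10.7% |

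The scores are therefore more exposed than CRM, where sampling error dominates. The direction of the bias is unknown. A bias in favour of L-ISR would make a non-inferiority conclusion easier to reach.

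**Step 3: the price of adjusting.** With equal groups and each surgeon doing half of all cases, the correlation between surgeon and group equals the share difference r. The variance of the adjusted group effect rises by 1/(1 − r²), before any gain from explained outcome variance.

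| r | 1/(1 − r²) | Per group for the precision of 72 |
|---|---|---|
| 0.2 | 1/0.96 = 1.04 | 75 |
| 0.4 | 1/0.84 = 1.19 | 86 |
| 0.6 | 1/0.64 = 1.56 | 113 |
| 1.0 | undefined | not estimable |

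**Step 4: event numbers.** Expected incomplete CRM: 72 × 0.061 + 72 × 0.081 = 4.4 + 5.8 ≈ 10 events. Over four surgeon-by-procedure cells, that averages 2 to 3 per cell.

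**The case against.** The strongest reply is that much of this is silence in a condensed article. Surgeon rostering, case report form items and covariate lists usually sit in the full protocol, the form itself or the analysis plan, none of which is shown. That is right as far as it goes. I do not claim that operating surgeon goes unrecorded or that it is missing from the Cox model. What remains is a stated method: for the scores and CRM the article names two-sample tests, and those have no place for surgeon.

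Stronger readings are tempting, and the article does not support them.

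- **One surgeon per procedure.** A reader might infer this from the surgeons operating independently. The sentence follows directly on the description of both groups, and its plain reading is that either surgeon may operate in either.
- **The surgeons differ in skill.** A reader might infer this from the learning-curve remark. That remark covers both operations in general, and section 2.3.1 describes both surgeons as experienced.
- **The centre lacks L-ISR experience.** A reader might infer this from the external L-ISR rate. Using a meta-analysis figure is a planning choice and says nothing about either surgeon.

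It is also fair to say that surgeon is one confounder among several when self-selected groups are compared with unadjusted tests. I agree that it belongs in the same adjusted model. It still needs naming, because patient and tumour covariates do not cover it, and because adjustment fails altogether if surgeon and procedure coincide.

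**Conclusion.** The concern holds in a limited form. With allocation by choice, two independent operators and no stated rule on surgeon mix, the named analyses of the primary scores and incomplete CRM leave a surgeon difference free to enter the procedure comparison. That it will do so is not shown, and its size cannot be derived from the document. The bias, rejection and precision figures above rest on assumed shares and surgeon effects, and the 5-point CRM difference is large against base rates of 6.1% and 8.1%. No conclusion is drawn for survival or recurrence. The remedy is simple enough to adopt without evidence that the surgeons differ.

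**What to change.** 1. **Section 2.7:** replace the unadjusted group comparisons as the main analysis. Include operating surgeon as a two-level fixed factor, alongside patient and tumour covariates, in the models for the QoL and functional scores. For incomplete CRM, use a Mantel–Haenszel risk difference stratified by surgeon. If the Cox covariates are set elsewhere, confirm there whether surgeon is among them.
2. **Section 2.3.1:** state whether both surgeons perform both procedures. If each does only one, say that the procedure effect cannot be separated from the surgeon effect.
3. **Reporting:** give the number of each procedure done by each surgeon. If the case report form does not already hold operating surgeon, add it.

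**Cost:** a few sentences, one data item and one model factor. The price in precision is that of step 3: small when shares are close, about 19% more variance at a 40-point difference. CRM results by surgeon and procedure should be labelled descriptive, since about 10 events over four cells cannot support inference.
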